**Table 1: Process Evaluation Components, Questions, and Indicators**

| Component                     | Questions                                                                                                                                                                                                                                                       | Indicators                                                                                                                                                                                                                                                                                                        |
|-------------------------------|-----------------------------------------------------------------------------------------------------------------------------------------------------------------------------------------------------------------------------------------------------------------|-------------------------------------------------------------------------------------------------------------------------------------------------------------------------------------------------------------------------------------------------------------------------------------------------------------------|
| Context                       | Has the standard of care changed to influence adherence or surveillance?
Have changes occurred that affect organizational capacity for performance?
Have users been exposed to biased messaging that may influence recruitment and/or protocol adherence? | 
 
Consistency of guidelines
 
CRF structural consistency: 
 
Staff & unit management consistency; staff ratios
 
 
 
Change in screening/enrollment
 
Feedback from sites
 
                    |
| Reach & Recruitment           | To what extent is the program reaching intended subjects?

Are unintended groups enrolled?                                                                                                                                                                | 
 
Screening records
 
Inclusion/exclusion compliance
 
Differences in intention-to-treat vs. per-protocol treatment of enrolled patients
 
                                                                                                            |
| Implementation:               | To what extent is the program implemented and received?                                                                                                                                                                                                         | 
 
CRF process consistency: Positioning assignment and maintenance; serial monitoring; and, 24-hour, discharge (or 7-day) and 90-day assessments
 
Neuroimaging enrollment fidelity
 
Protocol leader oversight records
 
Feedback from sites
 
 |
| Dose Delivered                | How much of the protocol is being administered?
What – if anything – is omitted or performed inconsistently?                                                                                                                                                 |                                                                                                                                                                                                                                                                                                                   |
| Dose Received                 | What is the average dose received?                                                                                                                                                                                                                              |                                                                                                                                                                                                                                                                                                                   |
| Overall Fidelity (Goal > 90%) | How well does project execution maintain fidelity of the original design?
- Aggregate structural compliance
- Aggregate process compliance                                                                                                                | 
 
CRF structural consistency
 
CRF process consistency
 
Blinding of endpoint measurers
 
                                                                                                                                                             |

We selected individual randomization as opposed to cluster randomization on the hospital/site level for three reasons. First, as emphasized by Murray, “the single most important factor in the power of a group-randomized trial is usually the number of groups.” Had we chosen cluster randomization, our sample size would need to increase from  $n=182$ , to  $n=5800$ , and this would demand at least 29 study sites to efficiently complete the study within 5 years. Given that the largest individually randomized thrombectomy trial included a maximum of 500 patients, and took over 3 years to complete at 16 sites, the conduct of a cluster randomized trial with an even larger thrombectomy sample would require considerable manpower and monetary support, much greater than can be provided. In addition, our 12 geographically widespread sites contribute diverse patients while delivering a consistent standard of care strictly managed by national guidelines, stroke center certification, and core measure requirements. Subject diversity is problematic in a cluster randomized design due to an inability to balance important patient traits. In trials involving a small number of clusters ( $\leq 10$  pairs), the loss of degrees of freedom resulting from pair matching becomes a particularly critical factor. Detailed investigation of this problem has led to the conclusion that for studies with a small number of clusters it is unlikely that effective matching can be possible and that “matching may be overused as a design tool.” In contrast, our use of individual (block) randomization will effectively balance patient traits and tPA treatment across protocols, considerably strengthening the evidence derived from this trial. Furthermore, if randomization would be determined on the hospital level, the attending physicians and nurses would know the protocol that would be applied to a patient before that patient is asked to give informed consent. Thus, group-randomization would open our study to enrollment selection bias due to differentially approaching patients that are deemed more/less likely to benefit from the pre-determined protocol for each hospital. This may, in fact, have contributed to enrollment of only small vessel strokes in HeadPoST. Group randomization would also challenge NIHSS/mRS score blinding. In summary,

cluster randomization would be a poor choice due to significant cost, the need for many more enrollment sites, and the oversight manpower required for optimal trial conduct, whereas use of individual randomization provides an economic, feasible and impactful approach to this study.

Data Capture and Control. The UTHSC Center for Biomedical Informatics (CBMI) provides the *RedCap* customized biomedical clinical-research informatics application for data entry. *RedCap* is a fully customizable integrated web-service for data collection with project alerts linked to an encrypted PostgreSQL database and is accessed via the Internet through secure web-applications. Site PIs are required to undergo UTHSC security clearance and training to receive a unique UTHSC ID for access to the *RedCap* system; each site PI will only be able to access data entered directly by them from their site. The study's clinical monitor will verify all data entered from each site against case report forms and electronic health record source data for accuracy; site investigators will be expected to resolve queries about missing data or suspected inaccuracies within 72 hours of notification. At each pre-specified interim analysis milestone, and at the time of the final analysis, research data will be bulk-exported to the ZODIAC biostatisticians who are fully independent from clinical trial enrollment. The national PI will not have access to the study database at any time during or after completion of the trial until an agreed upon post-publication time point.

UTHSC network and computing facilities are owned and managed by UTHSC-ITS; all CBMI systems are housed in the ITS computer center, which has electric power conditioning, UPS battery backup for short-term outages, and a backup diesel generator for long-term outages. The computer center also has fire suppression, temperature and humidity control, card key controlled access and video monitoring. Network traffic crossing the UTHSC network boundary is examined by a Cisco firewall against its Access Control Lists.

Neuroimaging files will be analyzed and archived by the UCLA Neuroimaging Core Lab under the direction of [name]. [name] and his staff will remain fully blinded to patient group assignment; the UCLA team will be responsible for sending all data directly to the ZODIAC statisticians for analysis. While ZODIAC does not incorporate formal imaging-based endpoints, imaging analyses will support protocol fidelity assessment (patient enrollments were consistent with inclusion/exclusion criteria) and will also aid in understanding differences found between groups once the study is complete.

### Endpoints.

Primary Endpoint: The percentage of patients with early neurologic deterioration (END) is our primary outcome. END is defined as a two or more point worsening ( $\geq 2$ ) in the NIHSS score in comparison to the time-0 NIHSS score at the time of positioning intervention termination (placement of the patient on the catheterization table or immediately prior to the time of elective induction/intubation for thrombectomy in centers utilizing general anesthesia). Not deteriorating (being stable) is defined as less than 2-point NIHSS worsening ( $< 2$ ) or NIHSS score improvement in comparison to the time-0 NIHSS score during the head position intervention.

We expect to see at most 5% of END participants in the 0° head position group, compared to 20% of END patients in the 30° head position group (15% lower deterioration). Our group-sequential design allows for early stopping due to futility or efficacy and is based on a two-sample two-sided proportion test as implemented in East 6.0 (Cytel, Cambridge, MA) with type I error  $\alpha=0.05$  and 80% power; it incorporates 3 interim analyses and 1 final look at the data which results in a sample size of  $n = 182$ . Interim analyses are planned with equal spacing after cases have been enrolled/observed for the primary endpoint (Table 2). The Lan-Demets alpha and beta spending approach with O'Brien-Fleming

boundaries are used both for futility and efficacy interim monitoring. Absence of primary endpoint evaluation will be counted as an END event so that all randomized participants will have a determined primary endpoint available for analysis, allowing for an intent-to-treat analysis with no primary endpoint attrition.

Analysis Plan for Aim 1 (primary efficacy endpoint); Hypothesis: *Patients with large artery occlusions placed in a 0°-HOB position will experience less early neurological deterioration than those in the 30°-HOB elevation group.* We will apply sequential testing in both patient groups (Table 2). As an example, the first look in the protocol is performed when 46 participants are enrolled/have their primary outcome evaluated; if the z-value associated with the test of equality of proportions in both arms is above 4.333 or below -4.333 the trial will be stopped early for efficacy (one group is clearly superior with respect to the primary outcome), whereas if that z-value is in the interval (-0.007, 0.007), the trial will be stopped early for futility (groups are essentially identical in outcome). If the z-value falls within the intervals (-4.333, -0.007) or (0.007, 4.333), the trial will continue until the next look at the data. Note that for the primary endpoint, absence of evaluation is counted as deterioration and that, consequently, all randomized participants will have a determined primary endpoint available for the analysis; therefore, intent-to-treat principles will support our primary data analysis. We will use unadjusted Cox proportional-hazards modeling to compare and Kaplan-Meier curves to visualize the rate of early neurological deterioration (> 2 NIHSS points change from baseline) in the two groups. The number at risk and censored in each group will be reported in the Kaplan-Meier survival curves every 10 minutes. Overall rates of END and according to group will be reported as frequencies and percentages and compared between groups with Fisher's Exact test. The number needed to harm will be estimated as the inverse of the absolute risk increase (ARI) = 1/ARI.

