Early neurologic deterioration is common in hyperacute ischemic stroke, ranging from 15% to 37.5% in large clinical trials, and selection of HOB positioning may play an important role in its occurrence. However, to date, clinical trial protocols exploring numerous drug and device interventions have remained silent on HOB positioning. Mechanisms proposed for clinical improvement at 0°-HOB include favorable gravitational arterial flow conditions, recruitment of collateral arterial blood flow routes, and in the case of intravenous thrombolysis, improved clot-lytic interactions augmenting arterial recanalization. Collectively, these mechanisms have caused many to argue that 0°-HOB positioning should be among the first steps taken in large artery hyperacute ischemic stroke patient management. The goal of this efficacy study is to determine if 0°-HOB positioning in hyperacute ischemic stroke prevents neurological symptom worsening in large artery occlusion patients. The study will achieve these goals through use of a novel protocol enabling enrollment of consecutive large artery occlusion patients while maintaining compliance with management specified by national guidelines, stroke center certification requirements, and U.S. core measures. We will enroll hyperacute large artery patients with salvageable brain early into stroke symptoms, that are candidates for mechanical thrombectomy (MT) (n=182). Patients will be randomized to one of two groups: 1) 0°-HOB positioning; or, 2) 30° HOB positioning. The primary endpoint will be early neurological deterioration (stroke symptom worsening) defined as an increase of 2 or more points from baseline (pre-intervention) National Institutes of Health Stroke Scale (NIHSS) score during the positioning period. These data will be employed to meet the following specific aims:

Aim 1 (primary efficacy endpoint): To identify if use of 0° HOB positioning is associated with clinical stability in hyperacute ischemic stroke. Hypothesis: *Patients with large artery occlusions placed in a 0° HOB position ( $V_1$ ), (superiority hypothesis), will experience less early neurologic deterioration within the time prior to thrombectomy, than those in the 30° HOB elevation group ( $V_c$ ), or  $H_0: V_1 = V_c$  versus  $H_A: V_1 < V_c$ .*

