#### Subject Screening, Enrollment, and Serial Monitoring (Figure)

Standard of Care: Suspected acute stroke patients will undergo guideline-supported standard of care stroke team emergency response procedures, including assessment/stabilization of airway, breathing, circulation, placement of a continuous pulse oximetry sensor, with immediate transport for imaging. The admission NIHSS will be scored on route to the imaging suite while the patient is in whatever position prehospital personnel have selected (this assessment is not utilized in the ZODIAC protocol but is a stroke center certification agency requirement). Continuous portable ECG monitoring with nasal cannula oxygen (if necessary, based on pulse oximetry) will be established in CT (or MRI), and IV access will be obtained with STAT blood draw; point of care testing will be conducted immediately before STAT non-contrast CT (or MRI) with CTA (or MRA). A rapid/detailed history/physical exam will be completed concurrently and patients eligible for treatment with tissue plasminogen activator (tPA) will have drug administered in CT (or MRI).

*Enrollment and Serial Monitoring:* Subjects meeting inclusions without exclusions will be consented and randomized. All subjects (0-degree and 30-degree) will be maintained at 0-degrees immediately after completion of neuroimaging. An NIHSS-certified practitioner naïve to the research protocol will measure the baseline/time 0 NIHSS score while the patient is at 0-degrees. The local investigator will then position the patient in the randomly assigned position and the serial NIHSS (every 10 minutes) monitoring phase of the intervention will begin. The site investigator must stay with the patient until positioned on the catheterization lab table to ensure assigned head position is maintained. The serial NIHSS monitoring phase ends immediately prior to placement on the catheterization lab table, with the primary endpoint measured during handoff by the same protocol naïve stroke team member to a protocol naïve catheterization lab practitioner certified in the NIHSS; in the case of elective procedural intubation, serial NIHSS monitoring will end immediately preceding the time of induction/intubation for thrombectomy. Of note, throughout execution of this protocol investigators must ensure that procedures do not delay time to tPA or time to catheterization for mechanical thrombectomy.

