All the safety outcome analyses will be executed in the intention-to-treat population. We will use unadjusted Cox proportional-hazards modeling to compare and Kaplan-Meier curves to visualize the rate of severe early neurological deterioration ( $> 4$  NIHSS points change from baseline) in the two groups. The number at risk and censored in each group will be reported in the Kaplan-Meier survival curves every 10 minutes. Overall and enrollment group rates of SND will be reported as frequencies and percentages and compared between groups with Fisher's Exact test. The number needed to harm for SND will be estimated as the inverse of the absolute risk increase (ARI) =  $1/\text{ARI}$ . Rates of hospital-acquired pneumonia, discharge, 90-day participant's death, post-discharge stroke, and symptomatic intracerebral hemorrhage post-reperfusion treatment will be reported in frequencies and percentages; these will be compared between groups using Fisher's Exact test together with odds ratios and the corresponding 95% confidence intervals and p-values from unadjusted logistic regression models that include randomization assignment as the predictor.

Pre-Specified Exploratory Endpoints: As discussed, END is the primary endpoint for this clinical trial and is measured proximally, at the termination of the intervention monitoring period. Our rationale for not utilizing a post-thrombectomy 90-day outcome is twofold: First, head positioning should not be deemed a "treatment" for LVO stroke; instead, head positioning is a rescue procedure similar to other medical care that is utilized to stabilize, optimize, and ensure both patient safety and optimal outcomes. The impact of a rescue procedure such as head positioning is best measured during the time it is implemented to determine its efficacy in supporting and optimizing patient condition. Second, thrombectomy is a highly effective definitive treatment for large vessel occlusion stroke patients. The tremendous effect size of thrombectomy may likely override any benefit of other interventions, including

head positioning, however this remains unknown at this time. In summary, we aim to determine the efficacy of head positioning as a simple rescue procedure, making measurement of END at the time of positioning on the catheterization lab table for thrombectomy (or immediately prior to elective induction/intubation in sites using general anesthesia for thrombectomy) our choice as the study primary endpoint.

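### The primary endpoint END is worded with two time windows, and the Cox/Kaplan-Meier analysis given the same name does not fit the better-supported one, the score at the end of positioning

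*Supplement*

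**What the plan says.** All references are to protocol version 2.0 in the Supplement.

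- **Specific Aims:** END is an "increase of 2 or more points from baseline (pre-intervention) National Institutes of Health Stroke Scale (NIHSS) score during the positioning period".
- **Endpoints, definition of END:** worsening of 2 or more points "in comparison to the time-0 NIHSS score at the time of positioning intervention termination", meaning placement on the catheterization table or just before elective induction.
- **Endpoints, next sentence:** a stable patient has less than 2 points of worsening, or "NIHSS score improvement in comparison to the time-0 NIHSS score during the head position intervention".
- **Enrollment and Serial Monitoring:** after positioning, "the serial NIHSS (every 10 minutes) monitoring phase of the intervention will begin". It ends just before placement on the table, "with the primary endpoint measured during handoff by the same protocol naïve stroke team member".
- **Pre-Specified Exploratory Endpoints:** "END is the primary endpoint for this clinical trial and is measured proximally, at the termination of the intervention monitoring period". The paragraph closes by again naming the time of positioning on the table, or just before induction, as the chosen measurement point.
- **Analysis Plan for Aim 1:** a sequential z-test of two proportions (Table 2), Fisher's exact test, and an unadjusted Cox model with Kaplan-Meier curves for END. There the event is written as a change of more than 2 points, and "The number at risk and censored in each group will be reported in the Kaplan-Meier survival curves every 10 minutes".

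No section defines the event time or the censoring time for the Cox and Kaplan-Meier analysis. None says how to classify a patient who worsens and then recovers before handoff.

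**The concern.** The event and its complement are described over different windows in adjacent sentences, and the Specific Aims side with the complement. Because scores are taken every 10 minutes, a transient worsening will be visible in the data, and someone will have to decide whether it counts.

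The survival analysis adds to the difficulty. Risk sets at 10-minute steps suit an outcome that can occur at any check. If END is the handoff score, it cannot. The binary comparison and the survival comparison could then rest on different events while both are reported as END. With about 23 events expected in 182 patients, reclassifying a few could matter to the result. An open choice of definition also leaves room to settle it after the data are known.

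**Working it through.** **1. One patient under each text.** Take a patient with a time-0 NIHSS of 12, a score of 14 at 20 minutes and 12 at handoff (illustrative scores).

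| Text | Classification |
|---|---|
| Specific Aims | END on the natural reading: a 2-point rise occurred during positioning |
| Endpoints, END sentence | not END: terminal change is 0 |
| Endpoints, stable sentence | not clearly stable: worsening during the intervention reached 2 points |
| Serial Monitoring and Exploratory Endpoints sections | not END: the handoff score decides |
| Aim 1 Cox/Kaplan-Meier | not an event at more than 2 points; at 2 or more points it depends on an event time that is not given |

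NIHSS scores are whole numbers, so more than 2 means 3 or more. A patient with exactly 2 points of worsening at handoff is END for the z-test and a non-event in the survival analysis as written.

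**2. The survival analysis under a terminal endpoint.** Each patient's event could fall only at his or her own last assessment. Everyone else is censored at their last assessment. The numbers at risk every 10 minutes would therefore mainly record how long patients took to reach the catheterization table.

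**3. The plan's own sample size.** Inputs from Endpoints: 5% vs 20%, two-sided α = 0.05, 80% power, four looks, N = 182.

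- n per arm = [1.96·√(2·0.125·0.875) + 0.8416·√(0.05·0.95 + 0.20·0.80)]² / 0.15² = (0.9167 + 0.3834)² / 0.0225 = 75.1, so 76.
- With continuity correction: 88 per arm, 176 in total.
- Inflation from the Table 2 efficacy bounds alone, by numerical integration: 1.020. 176 × 1.020 ≈ 180, close to 182.

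The calculation uses only the two rates. It cannot show whether 5% and 20% are terminal or any-time rates.

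**4. Hypothetical sensitivity.** Table 2 applied exactly at 23, 46, 69 and 91 per arm, pooled z, futility bounds applied. The documents give no rate of transient worsening, so every share below is assumed. Expected events = 91 × (sum of the two rates).

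(a) The planning rates are terminal and an any-time definition is used. Any-time rate = terminal rate + (1 − terminal rate) × share with transient worsening. For 5% in both arms: 0.05 + 0.95·0.05 = 9.75%, and 0.20 + 0.80·0.05 = 24%.

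| Transient share, 0° / 30° | Rates, 0° vs 30° | Events | Power |
|---|---|---|---|
| 0 / 0 | 5.0% vs 20.0% | 22.8 | 84% |
| 2.5% / 2.5% | 7.4% vs 22.0% | 26.7 | 75% |
| 5% / 5% | 9.8% vs 24.0% | 30.7 | 68% |
| 10% / 10% | 14.5% vs 28.0% | 38.7 | 56% |
| 5% / 10% | 9.8% vs 28.0% | 34.4 | 85% |
| 10% / 5% | 14.5% vs 24.0% | 35.0 | 33% |

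(b) The planning rates are any-time and the terminal definition is used. Terminal rate = any-time rate × (1 − share recovering by handoff).

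| Share recovering | Rates, 0° vs 30° | Events | Power |
|---|---|---|---|
| 10% | 4.5% vs 18.0% | 20.5 | 79% |
| 25% | 3.75% vs 15.0% | 17.1 | 71% |
| 50% | 2.5% vs 10.0% | 11.4 | 50% |

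The two definitions give the same events only if no worsening is transient.

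**The case against.** The strongest reply is that the documents largely settle the binary endpoint. The formal definition, the procedures and the endpoint rationale all point to the terminal score. The Specific Aims are a summary and do not say at any assessment; both uses of *during* can be read as change over the whole intervention. Table 2's test of proportions governs stopping, and the Cox model does not. This stands. A reader might infer that the stopping test has no defined input, and the documents do not support that.

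A reader might also infer that the trial is underpowered because repeated scoring gathers noise. With independent errors of 10–15% each way per score and 4 to 8 checks, calculated power would fall to about 76–59%. Those error rates are assumed. An eighth check is mentioned only for patients whose thrombectomy is cancelled (Decision Not to Treat), one team member appears to score serially, and site eligibility asks for inter-rater reliability of 97–100%. Reliability is not exact agreement, but it is the only rating-quality figure given and it lends the assumption no support. The direction is open too, as the unequal shares in the working show.

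Finally, it is tempting to say that the sample size was built on the terminal score, since the rates follow that definition on the page. The documents do not state it.

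What the reply leaves untouched is the literal mismatch in two places, the mismatch between more than 2 and at least 2 points, and a survival analysis without an event time.

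**Conclusion.** The inconsistency is real and remains in the current version. It changes which patients count as events in the stated analyses, so it is more than a slip of wording. The terminal score is the better-supported reading and should feed Table 2. The Cox/Kaplan-Meier analysis as described does not suit that endpoint and uses a different threshold.

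Confidence is high on the textual conflict. There is no supported estimate of its effect: the power figures depend wholly on assumed shares of transient worsening and on which definition the planning rates describe. They show that the choice could matter, and do not show that power is lost.

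**What to change.** 1. State END as worsening of at least 2 NIHSS points from time 0 at termination of positioning, in the Specific Aims, in both Endpoints sentences and in the Aim 1 plan. Correct the more-than-2 threshold.
2. Use only that binary outcome for Table 2 and Fisher's test.
3. Relabel the Cox/Kaplan-Meier analysis as a separate secondary outcome: time to first worsening of at least 2 points at any 10-minute assessment. Define its event and censoring times.
4. Report by arm how many patients worsened by at least 2 points and recovered before handoff.
5. Ask the sponsor to confirm whether 5% and 20% are terminal or any-time rates. If they are any-time rates, revisit the power statement for the terminal endpoint.

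The cost is protocol and analysis-plan wording, one added table row and one reply from the sponsor. The serial scores are already collected, so no new data are needed.

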**Randomization and power/sample size.** Our protocol utilizes two groups, 0°-HOB and 30°-HOB, and allows us to offer enrollment to consecutive eligible patients. To assure balance in the treatment group throughout the course of enrollment, we will use block randomization with a block size of 4 and an allocation ratio of 1:1. This scheme has been implemented in the *Unity* computerized enrollment procedure that only shows the random assignment for a single given participant to the user and may scramble subject enrollment numbers to ensure randomization balance. Future assignments cannot be predicted by study personnel because of the block assignment made together with assignments at all sites, and this effectively mitigates the risk for selection bias that might occur if anticipated group assignment were able to influence enrollment decisions.

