#### Plans for Interim Efficacy and Futility Analyses

ZODIAC is a efficacy study (Aim 1) that will determine superiority of one of two head positions in patients with large vessel occlusion hyperacute ischemic stroke prior to commencement of thrombectomy. Because the primary endpoint of clinical stability in and of itself constitutes a safety endpoint, we have developed a plan to examine both protocol efficacy and protocol futility with defined stopping boundaries (Table 2 repeated below). Using sequential testing, the DSMB will take a first look at data when 46 participants are enrolled and have had their primary outcome evaluated. For example, the DSMB will stop the trial for efficacy (with one group clearly superior) if the z-value associated with the test of equality of proportions is above 4.333 or below -4.333, whereas if that z-value is in the interval (-0.007, 0.007), the DSMB will stop the trial early for futility. However, if the z-value falls within the intervals (-4.333, -0.007) or (0.007, 4.333), the DSMB will continue the trial until the next look at the data when 92 participants are available. As described previously under the meetings section of this plan, the DSMB will hold regularly scheduled meetings based on achievement of these Table 2 enrollment milestones, and continue to assess efficacy and futility at each of these meetings until the point of trial completion is determined. The DSMB will formally report these findings to the PI, IRB, and NIH using the written report methods described above.

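### With 46 patients, the look-1 futility bound of ±0.007 acts as a rule to stop on a tie, and fires far more often than the boundary is meant to

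*Supplement*

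**What the plan says.** The Endpoints section of Protocol v2.0 describes a four-look design that "is based on a two-sample two-sided proportion test as implemented in East 6.0", with "type I error $\alpha=0.05$ and 80% power", planned event rates of 5% (0°) and 20% (30°), and 182 patients. Both sets of bounds are attributed to one method: "The Lan-Demets alpha and beta spending approach with O'Brien-Fleming" boundaries. Table 2 puts look 1 at 46 patients, with efficacy bounds ±4.333 and futility bounds ±0.007.

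The Analysis Plan for Aim 1 explains the look-1 rule: "whereas if that z-value is in the interval (-0.007, 0.007), the trial will be stopped early for futility (groups are essentially identical in outcome". The section on interim efficacy and futility analyses repeats it as a directive to the DSMB: "z-value is in the interval (-0.007, 0.007), the DSMB will stop the trial early for futility". Neither place calls the futility rule non-binding or says what to do if no events have occurred.

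On allocation, the randomization section says "we will use block randomization with a block size of 4 and an allocation ratio of 1:1". Blocks run across all sites together.

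**The concern.** A bound of ±0.007 on a continuous statistic defines a sliver that is almost never hit. A difference between two binomial proportions in 46 patients takes only a limited set of values. One of them is exactly zero, and it arises whenever the arms have the same number of events and the same size. At the event rates expected here, ties at 1, 2 or 3 events each are ordinary outcomes.

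The rule is also erratic. Two events in each arm of 23 stops the trial, whereas 2/22 v 2/24 gives |z| = 0.09 and the trial continues. Which applies depends on how the incomplete twelfth block falls. With no events in either arm, z is 0/0 and the plan gives no instruction.

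A tie is not evidence that the groups are alike. At 2/23 v 2/23 the Wald 95% interval for the difference is ±1.96 × √(2 × 0.087 × 0.913 / 23), or about ±16 percentage points. That still contains the 15-point effect the trial is built to detect.

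**Working it through.** **Inputs.** From Endpoints: 5% v 20%, two-sided α 0.05, β 0.20. From Table 2: looks at 46, 92, 138 and 182 and the bounds. From the randomization section: 1:1 in central blocks of 4. The per-arm count at look 1 is not stated and is derived below.

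**The plan's own figures.**
- Recursive integration of the Table 2 efficacy bounds alone gives two-sided α = 0.0500, so they control type I error without any futility stopping. With the futility bounds α is 0.0457.
- The fixed-sample size with continuity correction is 88 per arm. Times the efficacy-only inflation, 2 × 88 × 1.0196 = 179.4, within 3% of 182. The software settings are not given.
- The futility bounds reproduce (0.007, 0.375, 1.262 against 0.007, 0.374, 1.261) with the two-sided O'Brien-Fleming spending form and β = 0.20.

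**Intended look-1 futility risk at 5% v 20%.**
- Two-sided form: 4 × [1 − Φ(1.645/√0.25)] = 0.20%. The one-sided form is more generous: 2 × [1 − Φ(1.282/√0.25)] = 1.04%.
- Directly from the bound: the expected z at 23 per arm is 0.15/√(0.2075/23) = 1.58, where 0.2075 = 0.05×0.95 + 0.20×0.80. Then P(|Z| < 0.007) = 0.16%, or 0.17% with pooled variance. Under no difference it is 0.56%.

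**Split at 46 patients.** 46 = 11 × 4 + 2. The two patients drawn from the twelfth block fall one to each arm with probability 4/6, so the split is 23/23 in two thirds of cases and 22/24 or 24/22 in one sixth each.

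**What the rule does.** At 23/23 the smallest non-zero |z| is 0.295 (12 v 11 events), and 1 v 0 gives 1.01. So |z| < 0.007 means equal counts. At 22/24 it fires essentially only at 0 v 0, taken here as z = 0.

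**Exact probability at 5% v 20%, 23/23.** Σ P(X₁=k)·P(X₂=k), with X₁ ~ Bin(23, 0.05) and X₂ ~ Bin(23, 0.20):

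| Events in each arm | Probability |
|---|---|
| 0 | 0.0018 |
| 1 | 0.0126 |
| 2 | 0.0201 |
| 3 | 0.0130 |
| 4 | 0.0043 |
| 5 or more | 0.0009 |
| Total | 0.0527 |

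At 22/24 and 24/22 the probabilities are 0.0015 and 0.0022. Averaged: (2/3)(0.0527) + (1/6)(0.0015) + (1/6)(0.0022) = 0.0357. Leaving 0 v 0 out of the stops gives 0.034.

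**Other event rates** (assumed for illustration, not in the plan):

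| Rates | 23/23 | Averaged over splits |
|---|---|---|
| 5% v 15% | 10.7% | 7.4% |
| 12.5% both | 18.0% | 12.0% |
| 20% both | 14.7% | 9.8% |

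**Effect on the whole design**, other bounds unchanged:

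| Quantity | With look-1 futility | Without |
|---|---|---|
| Power, 5% v 20%, balanced looks (exact) | 83.5% | 86.7% |
| Power, 5% v 20%, blocks of 4 (simulated) | 84.7% | 86.8% |
| Power, 5% v 15%, balanced looks (exact) | 56.4% | 59.9% |
| Expected N, 12.5% both, balanced looks (exact) | 117 | 131 |
| Expected N, 12.5% both, blocks of 4 (simulated) | about 122 | 131 |

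Without the look-1 futility stop, exact type I error at balanced looks is 4.4% (12.5% both) and 4.7% (20% both).

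**The case against.** The best case for leaving the rule alone is that the design keeps its promises. Power stays above 80% and type I error is not inflated, so the excess sits in the look-1 increment rather than in the overall error budget. That is correct, and it limits how serious the point is. It is also true that 23/23 is not guaranteed, so 3.6% is the fairer headline than 5.3%. Removing the rule regains only about 2.1 of those 3.6 points, because roughly 40% of the trials it stops would have failed anyway. Under no difference, stopping early is the intended decision, so the 10–18% rates there are not errors in themselves.

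The DSMB section lets the board recommend changes to the stopping guidelines and vote on continuation, so a sensible board might override a tie. That does not cure the plan: both places that state the rule word it as a mandatory stop, and nothing calls it advisory. The saving under no difference is real, but it comes from stopping on ties that still leave a 15-point effect plausible.

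**Conclusion.** The concern holds. At the design rates the look-1 futility stop fires in 3.6% of trials averaged over block splits, and in 5.3% when the arms are 23/23. The boundary's normal-theory rate is about 0.17%, and the most generous reading of the beta spending is 1.04%. Even the averaged figure is about 21 times the first and more than three times the second. The price is about 2 points of power (3 with balanced looks), and the stop gives no type I error protection that the efficacy bounds lack.

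The averaged figures assume central permuted blocks with all orders equally likely. The power and sample-size results use the pooled z-statistic and treat 0 v 0 as z = 0. The conclusion does not depend on which spending form the software used: the one-sided form gives a look-1 bound of about 0.040, which would still fire only on exact ties at 23/23.

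This is a fault in the stopping rule, not a case of underpowering or inflated type I error. The summary of protocol changes records enrollment as closed, so the point concerns the plan as written.

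**What to change.** Remove the look-1 futility entry from both copies of Table 2, and the matching sentences from the Analysis Plan for Aim 1 and from the section on interim efficacy and futility analyses. Futility is then first assessed at 92 patients, with the existing bound |z| < 0.374. Keep the look-1 efficacy test and safety review. State that all futility bounds are non-binding; the efficacy bounds hold α = 0.05 without them, so no recalculation is needed. Say also how z is handled if neither arm has an event.

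A lighter alternative is to keep the table and only declare futility non-binding, so that the DSMB may disregard a tie. This removes the compulsion but leaves an uninformative trigger in the plan.

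The cost is a text and table edit. If the positions truly do not differ (12.5% in both arms), expected sample size rises from about 122 to 131 with blocks of 4, or from 117 to 131 with balanced looks, because accidental early stops disappear.
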